## Abstract

**Background:**

Post-stroke cognitive impairment is a common and severe complication of stroke, significantly affecting patients’ daily life and rehabilitation. Although transcranial direct current stimulation combined with computerized cognitive training has shown potential for improvement, current studies still have key limitations. Most have used only simultaneous intervention protocols, without systematically comparing sequential combination strategies, making it difficult to determine the optimal clinical approach.

**Objectives:**

The core objective of this study will be to address the existing research gap by comparing sequential intervention strategies and to resolve the key issue of identifying the optimal clinical approach.

**Methods:**

This study will use a single-center, double-blind, randomized controlled trial design. A total of 60 patients with post-stroke cognitive impairment will be randomly assigned in a 1:1:1:1 ratio to four groups: three intervention groups receiving computerized cognitive training combined with transcranial direct current stimulation at different timings (pre-training, concurrent, or post-training), and one sham control group. All interventions will be administered five times a week for two consecutive weeks. Follow-up assessments will be conducted at 4 and 12 weeks post-intervention.

**Discussion:**

This trial will systematically evaluate the optimal timing strategies for combining tDCS and CCT in PSCI. The hypothesized mechanisms are: (1) synchronous stimulation enhancing cognitive processing efficiency through immediate synaptic changes, (2) pre-training stimulation promoting plasticity via long-term potentiation-like modifications, and (3) post-training stimulation consolidating training effects by modulating neuronal synchrony. High-sensitivity cerebral oxygenation parameters will be used to assess microcirculatory improvements, linking physiological changes to cognitive recovery. However, ceiling effects and test biases will potentially limit the accuracy of long-term results, while sample size and lack of stratification based on brain lesion characteristics may introduce heterogeneity. Future studies will need to incorporate multimodal neuroimaging for stratified analysis and should develop personalized interventions based on lesion severity, disease stage, and timing to address therapeutic challenges and advance precision rehabilitation.

**Trial registration:** ChiCTR2500102565.[Chinese Clinical Trial Registry (ChiCTR), https://www.chictr.org.cn/] [Registered on May 16, 2025]

## Introduction

Stroke, the second leading cause of death worldwide, significantly affects patients and their families due to its high incidence and severe long-term consequences [1].Survivors often experience lingering motor, sensory, cognitive, and bowel/bladder dysfunctions, which reduce their quality of life, impose a significant economic burden on society, and cause emotional strain on families [2,3].International studies show that the incidence of post-stroke cognitive impairment (PSCI) in the Chinese population can reach 78.7% within 3 months post-stroke [4].Cognitive impairments, including severe declines in memory, attention, and executive function, make it difficult for patients to perform daily tasks. The distress caused by these impairments can sometimes outweigh that of physical disabilities, complicating rehabilitation and hindering overall recovery. Given the multidimensional impact of cognitive dysfunction on rehabilitation, cognitive recovery should be prioritized as highly as physical restoration [5,6].

The James Lind Alliance, a UK-based partnership for setting research priorities, has identified PSCI as a top priority in stroke research [7].The 2021 joint guidelines from the European Stroke Organisation and European Academy of Neurology highlight the ongoing therapeutic limitations of cognitive training for PSCI. To overcome this challenge, the guidelines emphasize the need for prioritizing randomized controlled trials in future research [8].Computerized cognitive training (CCT) is a software-based intervention delivered through digital platforms, known for its engaging interface, portability, and real-time progress tracking. This approach has gained popularity in clinical practice and shown significant therapeutic efficacy in cognitive impairment rehabilitation [9].Its potential benefits may arise from the interaction between cognitive-psychological changes induced by CCT and dopamine neurotransmitter release [10].However, its use as a standalone treatment for PSCI patients shows limited clinical efficacy in certain populations [11].This limitation arises from CCT’s unimodal design (e.g., visual tasks), which restricts the activation of multimodal neural circuits and hinders neuroplasticity. Additionally, standalone CCT provides short-term cognitive benefits but struggles to generalize domain-specific improvements to overall functional gains [12].

To overcome these limitations, combining therapy with non-invasive brain stimulation has become a key research focus. Transcranial Direct Current Stimulation (tDCS) is especially prioritized due to its safety profile—it does not induce action potentials, which significantly reduces the risk of seizures and ensures treatment safety [13].Additionally, tDCS effectively modulates cortical excitability, addressing CCT’s limitations by regulating neuroplasticity in a targeted manner, thereby creating a ‘neuroactivation-cognitive enhancement’ feedback loop [14,15].tDCS also exhibits significant long-lasting aftereffects, with 20–30 minutes of stimulation maintaining neural network modulation for up to 90 minutes post-treatment, thereby providing a neurobiological basis for sustained cognitive enhancement [16].However, most devices lack real-time monitoring and adaptive parameter adjustments (e.g., stimulus intensity), which limits their regulatory efficacy beyond simple intervention-based stimulation.

Current evidence suggests that combined therapy typically enhances efficacy compared to monotherapy, though study conclusions remain inconsistent.Chen et al. [17]observed significantly improved vascular vasomotor function in the combined therapy group via transcranial Doppler ultrasonography, linked to optimized hippocampal activation patterns and a bidirectional beneficial cycle between vascular and cognitive functions. Notably, Kolskar et al. [18] reported no additional benefits of tDCS-CCT combinations over CCT alone in high-reliability fMRI-based brain activation analyses.Meanwhile, studies confirm significant differences in clinical outcomes between combined strategies.Naro et al. [19]found both concurrent tDCS-RAGT and sequential RAGT-then-tDCS interventions in stroke patients significantly improved balance (p < 0.001) and moderately enhanced gait endurance (p = 0.04), with the sequential approach showing particularly sustained effects—contradicting Leon’s null findings [20].Current investigations into tDCS-CCT combinations highlight potential cognitive benefits, yet their efficacy remains inconsistent [21].A meta-analysis confirmed significant improvements in working memory with CCT in stroke patients, but there were insufficient tDCS studies for analysis, and meta-regression identified no significant moderators.Given that tDCS and CCT exhibit complementary mechanisms of action and that controversy exists regarding the efficacy of combined tDCS at different time sequences., we will propose combining these interventions to address cognitive impairments in stroke patients [22].

Given the significant gap in research on combined tDCS-CCT intervention strategies, particularly the lack of systematic exploration into the differential effects between simultaneous and sequential intervention modes, this study will investigate the cognitive intervention effects of tDCS in stroke patients undergoing CCT. The primary objective will be to compare efficacy differences across various temporal combinations of tDCS-CCT therapies to identify the optimal synergistic protocol. Rooted in the theoretical framework linking tDCS-mediated cerebral hemodynamic modulation to cognitive enhancement, the study will specifically examine the association between prefrontal cortical oxygen metabolism and cognitive improvement. Functional Near-Infrared Spectroscopy (fNIRS) will be used to dynamically monitor pre- and post-treatment hemodynamic parameters in the prefrontal cortex, aiming to elucidate the neurophysiological mechanisms underlying cognitive recovery through the lens of neurovascular coupling.

## Methods and design

The study protocol was approved by the Scientific Research Ethics Committee of Nanshan District People’s Hospital, Shenzhen (Approval Number: Scientific Ethics Review ky-2024 103101, Approval Date: March 5, 2025), and registered with the Chinese Clinical Trial Registry (ChiCTR) prior to the initiation of the study (Registration Number: ChiCTR2500102565, Registration Date: May 16, 2025)https://www.chictr.org.cn/. All study activities will be conducted in accordance with the requirements of the ethics committee, and the validity of the study protocol will cover the entire duration of the research (until March 5, 2026).

This study will be in the participant recruitment phase, which is expected to be completed between June 2025 and July 2026. At the time of submission, data collection has not yet commenced. As a study protocol, this manuscript will aim to describe the planned study prior to the generation of any results.

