### Study setting and recruitment

Patient recruitment will be conducted at the Department of Rehabilitation Medicine, Shenzhen Nanshan People’s Hospital, from June 2025 to July 2026, using a dual approach to optimize eligibility assessment and engagement. Outpatient recruitment will utilize posters in the rehabilitation clinic, enabling interested patients to notify therapists for referral to the principal investigator for preliminary screening. Concurrently, resident physicians in the Neurology and Rehabilitation Medicine Departments will systematically screen inpatients against predefined criteria and refer eligible candidates to the research team for formal enrollment. All referring clinicians will undergo standardized protocol training to ensure consistency, and written informed consent will be obtained prior to participant inclusion. Eligibility criteria are detailed below.

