### Interventions

All participants will receive five sessions per week for two weeks, totaling 10 sessions. Adverse events will be monitored during each session, with researchers administering tDCS stimulation according to Brunoni et al.‘s protocol [23] to assess patient discomfort, pain, and any causality related to tDCS. Four treatment groups will be established:

Group A (tDCS-before-CCT): Patients will receive 20 minutes of tDCS, followed by 30 minutes of CCT after a 4-hour interval.Group B (tDCS-after-CCT): Patients will complete 30 minutes of CCT first, then will receive 20 minutes of tDCS after a 4-hour interval.Group C (tDCS-with-CCT): tDCS will be administered concurrently during the last 20 minutes of the 30-minute CCT session.Group D (CCT-only/Sham): Patients will undergo CCT with simultaneous placebo tDCS (sham stimulation).

Prior to the treatment intervention, patients will undergo a baseline assessment to determine eligibility. Enrollment will be based on the Montreal Cognitive Assessment (MoCA) [24]. Assessors will be blinded to group allocation. Post-treatment assessments will be conducted immediately after treatment completion, with follow-up assessments scheduled at 4 and 12 weeks post-treatment.The use of any non-invasive brain stimulation protocols other than those explicitly specified in this study (e.g., transcranial magnetic stimulation [TMS]) is strictly prohibited throughout the research period.

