### Safety and adverse event monitoring

Participant safety will be monitored continuously throughout the 1-week intervention period and the 2-month follow-up phase. All adverse events (AEs) and serious adverse events (SAEs) – whether reported by participants or observed by study investigators – will be systematically documented in accordance with established clinical research protocols.To monitor and manage adverse effects, patients will report sensations of itching, tingling, burning, headache, or other discomforts using a 4-point scale (1 = absent, 2 = mild, 3 = moderate, 4 = severe). The causal relationship between symptoms and tDCS stimulation will be assessed on a 5-point scale (1 = unrelated, 5 = strongly related).In the event of adverse events (AEs) or serious adverse events (SAEs), investigators shall provide immediate appropriate medical intervention and conduct follow-up assessments until clinical resolution or stabilization is confirmed. SAE data will be formally reported during regular meetings of the Data Safety Monitoring Board (DSMB) in compliance with institutional safety protocols.

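### The protocol's stated validity date falls several months before its own schedule ends, and its stated safety-monitoring window stops short of the last visit

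*Protocol article*

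**What the plan says.** **Validity date.** Under Methods and design, the protocol article gives the ethics decision as "Approval Date: March 5, 2025" and states that "the validity of the study protocol will cover the entire duration of the research (until March 5, 2026"). The same sentence promises that "All study activities will be conducted in accordance with the requirements of the ethics committee".

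**Schedule.** The next paragraph of that section describes recruitment as a phase "which is expected to be completed between June 2025 and July 2026". Study setting and recruitment gives the window plainly, "from June 2025 to July 2026". Interventions sets the time per patient: "All participants will receive five sessions per week for two weeks, totaling 10 sessions", "with follow-up assessments scheduled at 4 and 12 weeks post-treatment".

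**Safety window.** Safety and adverse event monitoring states: "Participant safety will be monitored continuously throughout the 1-week intervention period and the 2-month follow-up phase". Three other sections bear on this:
- Interventions has adverse events monitored at each session.
- Data management has adverse events tracked during treatment, and lists only the cognitive scales for the 3-month follow-up.
- Optimizing retention and follow-up adherence gives every patient a 3-month follow-up plan, with staff contacting them two days before each appointment.

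**The concern.** Both items are figures that site staff would act on, and each conflicts with the schedule elsewhere in the article.

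On the first, staff following the recruitment and visit schedule would enrol, treat and assess patients after the date on which the article says the research ends. Whatever the date refers to, it is wrong for that schedule or its meaning is not explained. If it is the ethics approval term, activity after it would need an extension.

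On the second, both parts of the safety window disagree with the trial's design: one week against two for treatment, and two months against 12 weeks (or 3 months) for follow-up. Read as written, planned adverse event monitoring stops before the trial's last assessment. Data management does not close that gap, because its adverse event tracking is tied to the treatment period.

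**Working it through.** This is calendar arithmetic. Month-only dates are bounded by the first and last day of the month.

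**Inputs**
- Stated end of validity: March 5, 2026 (Methods and design).
- Ethics approval: March 5, 2025 (Methods and design).
- End of recruitment: July 2026, taken as July 1 to July 31 (Methods and design; Study setting and recruitment).
- Treatment: 2 weeks = 14 days (Interventions).
- Last visit: 12 weeks = 84 days after treatment (Interventions).
- Stated safety window: 1 week = 7 days, plus 2 months, taken as 56 days (8 weeks) to 62 days (two long calendar months).

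**What the stated date matches.** March 5, 2025 to March 5, 2026 is 365 days, exactly one year from approval. The recruitment and follow-up schedule does not produce this date.

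**Validity date against schedule.** Last visit = last enrolment + 14 + 84 = last enrolment + 98 days.

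| Last enrolment | Days after March 5, 2026 | Last 12-week visit | Days after March 5, 2026 | Months (÷ 30.44) |
|---|---|---|---|---|
| July 1, 2026 | 118 | October 7, 2026 | 118 + 98 = 216 | 7.1 |
| July 31, 2026 | 148 | November 6, 2026 | 148 + 98 = 246 | 8.1 |

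Recruitment alone overruns the date by 118 to 148 days, or about 4 to 5 months.

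**Sensitivity**
- If the 12 weeks are counted from baseline, the gap is 118 + 84 = 202 to 148 + 84 = 232 days (6.6 to 7.6 months). The contradiction remains.
- Ten weekday sessions span 11 to 13 days from first to last, depending on the starting weekday, so the 14-day figure can be 1 to 3 days too long. A delay between enrolment and first session works the other way. Neither matters on a scale of months.
- For the stated date to hold, the last patient would have to enrol about 98 days before March 5, 2026, at around the end of November 2025. That is roughly 8 months before the end of July 2026.

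**Safety window against the 12-week visit**
- Two months counted from the end of the 2-week treatment: 84 − 62 = 22 days to 84 − 56 = 28 days short (3.1 to 4.0 weeks).
- One week plus two months counted literally from the first session: 98 − (7 + 62) = 29 days to 98 − (7 + 56) = 35 days short (4.1 to 5.0 weeks).
- Full range: 22 to 35 days, or about 3 to 5 weeks.

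**The case against.** A reader might infer that patients will be treated without valid ethics approval. The article does not support that. It attaches the validity to the study protocol, so reading it as the approval term is an inference from the one-year interval. If it is an approval term, renewal would be the obvious course, and the article commits all activities to the ethics committee's requirements. A condensed article commonly leaves continuing review to the full protocol and the ethics file, so silence does not show that no extension exists. That objection stands. It limits the consequence, but a renewable one-year term still does not cover the whole research as the sentence claims.

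A reader might also infer that the second treatment week goes unmonitored, or that late adverse events are lost. Neither follows. Interventions has monitoring at every session, and Data management tracks events throughout treatment, so the one-week figure looks like a drafting slip. The safety section documents any event reported by a participant or observed by an investigator, and the section on the data monitoring committee sends serious events to the department director within 48 hours. Patients are still encouraged to attend the 12-week visit in person. What remains is narrower: the stated period of active monitoring is too short, over 3 to 5 weeks after treatment has ended.

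Finally, the 7 to 8 months depends on the last patient enrolling in July 2026. The wording in Methods and design could allow recruitment to finish sooner. That is fair, and the figure should be read as conditional. The planned window nevertheless runs to July 2026, and its last months lie wholly after the stated date.

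**Conclusion.** Both inconsistencies stand, and nothing in the article reconciles them.

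- **Validity date.** March 5, 2026 does not cover the planned schedule. The overrun is several months, and about 7 to 8 months if the last patient enrols in July 2026 and the 12 weeks run from the end of treatment. Whether any patient would fall outside ethics approval cannot be decided from the article.
- **Safety window.** Active adverse event monitoring, as stated, ends roughly 3 to 5 weeks before the 12-week visit. The range reflects how the one-week and two-month figures are read. Treatment sessions are covered.

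This matters for regulatory clarity and participant safety. It has no bearing on type I error, power or the treatment comparison.

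**What to change.** 1. In Methods and design, correct the date and say what it refers to: the ethics approval term, the protocol's validity or something else.
2. Before enrolling or continuing patients beyond March 5, 2026, confirm that any extension needed is in place, or obtain it, through the last patient's 12-week visit. That means early November 2026 if recruitment uses all of July, with some margin for late visits.
3. In Safety and adverse event monitoring, restate the window as the 2-week intervention plus the 12-week follow-up.
4. Align Data management with that window, so that adverse events are collected through follow-up and not only during treatment.
5. Ask about adverse events at the existing 12-week visit, or at the contact already planned two days before it for patients assessed remotely.

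The cost is a few wording changes, slightly longer adverse event collection at a contact that already takes place, and possibly one extension request. Arms, sample size and analysis do not change.

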### Study design

This is a single-center, double-blind, randomized controlled exploratory trial. Sixty patients will be randomly assigned to one of four groups (n = 15 per group). The protocol will be reported following Standard Protocol Items: Recommendations for Interventional Trials (SPIRIT) schedule statement(S1 File).Participant enrollment, randomization, assessment, and follow-up schedules are summarized in **Fig 1**.For a detailed visualization of the study workflow, **Fig 2**, which outlines the sequential steps from participant recruitment to final follow-up.

**Fig 1 pone.0342761.g001:**
[figure not shown]
Trial schedule of enrollment, intervention, and assessments. Trial schedule of enrollment, intervention, and assessments.MoCA,Montreal Cognitive Assessment; MMSE,Mini-Mental State Examination; HAMA,Hamilton Anxiety Scale; HAMD,Hamilton Depression Rating Scale;MBI,Modified Barthel Index; tDCS,Transcranial Direct Current Stimulation; CCT,Computerized Cognitive Training; fNIRS,Functional Near-Infrared Spectroscopy; VFT,Verbal Fluency Test.

**Fig 2 pone.0342761.g002:**
[figure not shown]
The CONSORT (Consolidated Standards of Reporting Trials) flowchart for clinical trials.

### Study setting and recruitment

Patient recruitment will be conducted at the Department of Rehabilitation Medicine, Shenzhen Nanshan People’s Hospital, from June 2025 to July 2026, using a dual approach to optimize eligibility assessment and engagement. Outpatient recruitment will utilize posters in the rehabilitation clinic, enabling interested patients to notify therapists for referral to the principal investigator for preliminary screening. Concurrently, resident physicians in the Neurology and Rehabilitation Medicine Departments will systematically screen inpatients against predefined criteria and refer eligible candidates to the research team for formal enrollment. All referring clinicians will undergo standardized protocol training to ensure consistency, and written informed consent will be obtained prior to participant inclusion. Eligibility criteria are detailed below.

### Participants

#### Inclusion criteria.

(a)Diagnosed with stroke (intracerebral hemorrhage or cerebral infarction) confirmed by head CT/MRI, per the 1995 Fourth National Cerebrovascular Disease Conference criteria;(b)Alert, hemodynamically stable, and capable of completing cognitive assessments;(c)First-time stroke within 3 months post-onset;(d)MoCA score between 10–26 (inclusive);(e)Voluntary informed consent.

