#### Exclusion criteria:.

(a)History of other neurological disorders (e.g., Parkinson’s disease, tumors, hydrocephalus, or trauma);(b)Cognitive impairment attributable to non-stroke conditions;(c)Significant auditory/visual deficits, aphasia, or uncooperativeness;(d)Pre-stroke cognitive decline.

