### Outcome measures

#### Primary outcomes.

MoCA: will be administered at baseline, 4 weeks, and 12 weeks, with a focus on detecting mild cognitive improvements. The cutoff scores for cognitive impairment will be determined based on educational attainment (e.g., ≤ 13 points for primary education, ≤ 19 points for secondary education, and ≤24 points for tertiary education, as per the MoCA-Chinese version criteria).Prefrontal Cortex (PFC) Activation (fNIRS): Task-related oxygenated hemoglobin (HbO) signals will be measured using the NirSmartⅡ-3000D system (Huichuang Medical, Danyang), with wavelengths of 730 nm/850 nm and a sampling rate of 11 Hz. The channel configuration will consist of 22 channels using 8 emitters and 8 detectors (3 cm separation), aligned with the EEG 10–20 system (**Fig 4**).The protocol includes 8 minutes of resting-state data (eyes closed, seated comfortably in a quiet room). The Verbal Fluency Task (VFT) will involve 30 seconds of pre-task rest, 60 seconds of task phase (generate words starting with |d|, |g|, or |h|; 20 seconds per phoneme), and 75 seconds of post-task rest. The outcomes will include PFC activation intensity, resting-state functional connectivity (left/right PFC), and word-generation accuracy.

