Methodological limitations must be considered: neuropsychological testing is susceptible to ceiling and practice effects in longitudinal designs. High-functioning patients may experience premature plateaus (“ceiling effect”), while low-functioning individuals may show artificial improvements due to repeated exposure (“practice effect”), complicating the assessment of true intervention effects.Notably, inter-individual variance in lesion site and severity will modulate treatment response; we will therefore integrate baseline imaging—lesion location and volume—for subgroup analyses to craft interventions that concurrently respect lesion signature, disease stage and temporal order. As evidence on the tDCS–CCT pairing will remain sparse and prior cohorts will have been small, heterogeneity will persist; thus, the forthcoming findings will generalize only to the single-center Chinese cohort to be recruited here, and subsequent larger, geographically dispersed trials will be required to validate this sequential strategy.

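### The MoCA 10–26 entry range conflicts with the protocol's own education-specific cutoffs for cognitive impairment, so some patients counted as PSCI need not meet its definition

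*Protocol article*

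**What the plan says.** Four statements in the protocol article bear on who counts as having post-stroke cognitive impairment.

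- **Population.** The abstract (Methods) states: "A total of 60 patients with post-stroke cognitive impairment will be randomly assigned".
- **Entry rule.** Inclusion criterion (d) is "MoCA score between 10–26 (inclusive"), with no reference to education. The Interventions section confirms which test decides entry: "Enrollment will be based on the Montreal Cognitive Assessment (MoCA").
- **Definition of impairment.** Under Primary outcomes: "The cutoff scores for cognitive impairment will be determined based on educational attainment". The values given are "≤ 13 points for primary education, ≤ 19 points for secondary education, and ≤24 points for tertiary education".
- **Other criteria on cognition.** The exclusion criteria remove "Cognitive impairment attributable to non-stroke conditions" and decline that predates the stroke. Both concern the cause or timing of impairment. Neither requires that impairment be present.

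The Discussion also warns that "neuropsychological testing is susceptible to ceiling and practice effects in longitudinal designs", without relating this to the entry range.

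**The concern.** The protocol uses two different thresholds on the same scale. One decides who enters and the other decides who is impaired, and the first is the more permissive at every education level. A patient can therefore meet every inclusion criterion, be randomised, and be reported as a PSCI patient while scoring as unimpaired under the protocol's own cutoffs.

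What is at stake is mainly the population to which the result applies. The trial is meant to say which timing of stimulation and training works best in PSCI. If an unknown part of the sample is outside that definition at baseline, the conclusion does not describe that part. If such patients also respond less, the average difference between arms would shrink. MoCA is both the entry test and the outcome on which the sample size rests, so the entry range also fixes where patients start on the primary scale.

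**Working it through.** The plan gives no calculated figure on this point, so there is none to reproduce. The check counts scores and then asks what can be said about patients.

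**Inputs.** Entry range 10 to 26 (Inclusion criteria). Cutoffs 13, 19 and 24 (Primary outcomes).

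**Step 1: admissible scores.** 26 − 10 + 1 = 17 integer values, the same for everyone.

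**Step 2: admissible scores above the cutoff c.** The count is 26 − c.

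| Education | Cutoff | Eligible but above cutoff | Count | Share of 17 | Left if entry also required a score at or below the cutoff |
|---|---|---|---|---|---|
| Primary | 13 | 14–26 | 26 − 13 = 13 | 76% | 10–13 (4 scores) |
| Secondary | 19 | 20–26 | 26 − 19 = 7 | 41% | 10–19 (10 scores) |
| Tertiary | 24 | 25–26 | 26 − 24 = 2 | 12% | 10–24 (15 scores) |

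The overlap of the three eligible-but-unimpaired ranges is 25–26.

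**Step 3: does another criterion close the gap?** The remaining inclusion criteria cover the stroke diagnosis, alertness and ability to be tested, a first stroke within 3 months, and consent. The MMSE has a threshold for normal cognition, but it is a secondary outcome and not an entry test. Nothing stated requires impairment.

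**Step 4: from scores to patients.** Let p be the share of patients above their cutoff, d the between-arm effect in the others and d_u the effect in those above the cutoff. The average effect is (1 − p)·d + p·d_u. If d_u = d there is no dilution. If d_u = 0 the effect is reduced by the fraction p. The article gives no education mix, no baseline MoCA distribution and no effect by impairment status, so neither p nor d_u is known and the size of any dilution cannot be computed.

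**Step 5: would power suffer?** As an illustration only, assume d_u = 0, so that the planned f = 0.708 becomes 0.708·(1 − p). Take N = 48, four groups, three measurements and correlation 0.30, with 6 and 88 degrees of freedom.

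- With the standard within-between interaction noncentrality, f²·N·3/(1 − 0.30), even p = 0.5 (f = 0.354) gives 0.1253 × 48 × 3/0.70 = 25.8 and power 0.975.
- With noncentrality f²·N, the one variant tried that returns the plan's 48, power is 0.964 at p = 0, 0.824 at p = 0.2 (f = 0.566) and 0.377 at p = 0.5.

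The answer depends on the formula as well as on two unknown inputs, so no statement about lost power follows.

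**The case against.** The strongest defence is that the cutoffs were never meant for entry. They are introduced as examples and sit under outcome measures, apparently to classify scores. The range 10–26 may be a severity window applied to patients already diagnosed with PSCI. The article does not rule this reading out, but it does not state it either. Even as a classification, the cutoffs are called cutoffs for cognitive impairment, and applying them at baseline would label some enrolled PSCI patients unimpaired. The need to reconcile the sections stands on either reading.

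A second defence is that the analysis absorbs part of the problem. The mixed model lists baseline score and education among its example covariates, which can reduce noise. Randomisation means that patients above their cutoff do not bias the comparison between arms. The trial is called exploratory, and the Discussion limits generalisation to the recruited cohort. All of this stands. None of it makes an unimpaired patient part of the PSCI population.

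Three stronger inferences are tempting and are not supported.

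- **That 76%, 41% or 12% of patients are unimpaired.** These are shares of score values. Nothing in the document says how patients are spread over them.
- **That the effect is diluted by a known amount, or that the trial is underpowered for this reason.** Any percentage for p is an assumption, and so is zero response above the cutoff.
- **That the whole above-cutoff group suffers from a ceiling.** The Discussion says "High-functioning patients may experience premature plateaus (“ceiling effect"), but a primary-educated patient who scores 14 or 20 is not near the top of the range. The ceiling argument applies only around 25–26. The article does not state the MoCA maximum, so no headroom figure is given here.

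**Conclusion.** The conflict is real and exact. The upper entry limit of 26 exceeds all three of the protocol's impairment cutoffs, no other stated criterion requires impairment, and the population is nevertheless described as PSCI. This is a contradiction between stated rules, not a detail left to another document.

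Its certain consequence is that the plan, followed as written, can enrol and report as PSCI patients who do not meet its own definition. How many cannot be determined. Dilution is plausible in direction if such patients respond less, but its size is unknown. The ceiling effect is limited to scores near 25–26. The conclusion assumes that the cutoffs mean what the outcome section calls them, and that the article states all criteria on cognition. It is worth correcting, but it does not threaten the validity of the randomised comparison.

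**What to change.** Reconcile the inclusion criteria with the outcome section so that one definition of impairment governs who is called PSCI. Which definition that is remains the sponsor's choice.

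**If the flat range is kept:**

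1. Describe the population as stroke patients with MoCA 10–26, in the abstract, objectives and conclusions.
2. Report by arm the number of patients above their education-specific cutoff at baseline.
3. Pre-specify a sensitivity analysis of the primary MoCA comparison limited to patients at or below their cutoff. Membership depends only on baseline MoCA and education, so the subset comparison remains a randomised one. Both variables are already named as model covariates.

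The cost is a little more analysis work and lower precision in the subset, which starts from only 15 patients per arm. Recruitment is unaffected, and the text can be fixed at any time before database lock and unblinding.

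**If entry is restricted to the cutoffs instead,** the population matches its label, but the screening pool shrinks substantially among less-educated patients: 4 of 17 scores remain for primary education and 10 of 17 for secondary. The sample would also shift towards lower scores in those groups. At a single centre that needs 60 first-stroke patients within 3 months of onset, this is a serious recruitment cost to weigh. The change is cleanest before the first patient is enrolled; the article says data collection had not begun at submission.
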